## f. Procedures: intervention phase

*Consent procedure intervention phase:*

Prior to the implementation of the interventions, meetings will be organised with the district commissioner, officers and chiefs with the district health team to seek approval for the study. Sensitization of communities will be done by chiefs and assistant chiefs and village elders from the study area. Community meetings (barazas) will be held in the selected areas and study staff will explain the purpose of the study, the procedures to be followed and the risks and benefits of participation. Information sheets shall be provided in English, DhoLuo, and Kiswahili to all district representatives, chiefs and households (Appendix A).

All consent forms will be available in English, DhoLuo, or Kiswahili. Translations will be checked through back-translation (Appendix B). Before the targeted distribution of LLINs and IRS, informed consent will be obtained at the household level from the head of the household; this will be recorded by signature or thumb-print which is then overseen by the signature of an independent witness. Before FSAT, informed consent will be obtained at the individual level; this will be recorded by signature or thumb-print accompanied by the signature of an independent witness of selected individuals and/or their parents/guardians. Assent forms will be signed by children between the ages of 13 and 17 years and by their parents/guardians. Each assent form will be accompanied by consent form signed by the parent/guardian.

Larviciding will be done after consulting with and receiving approval from the DOMC and PCPB and after community meetings. Verbal consent will be sought from any privately owned permanent breeding sites in the intervention areas (e.g. fish ponds) after distributing information sheets. Since most mosquito breeding sites are not necessarily restricted to certain households and larviciding should be seen as a community intervention [21-22] [21], consent at household level is not practical and approval from the community, DOMC and PCPB will be sought instead.

*Timing of the intervention:*

March-May 2012

The first round of interventions in all targeted hotspots will be completed before the start of the transmission season in May 2012. IRS, LLINs, larviciding and FSAT have the largest predicted impact if started before the start of the transmission season [19]. Follow-ups for LLIN coverage and usage will occur 1 and 6 months after initial distribution (see table in section 11). Clusters will be randomly allocated to the intervention or control arm. Based on a trial in Kwale District, Coast, a public randomization approach will be used to encourage participation among the community and to promote transparency of the selection procedure (Brooker et al., 2010). Meetings will be called with district officials, chiefs, community stakeholders and elders to explain the purpose and visually demonstrate the randomization process.

Depending on the outcomes of the first year of the intervention, in consultation with the DOMC, we aim to roll-out the most efficacious intervention/s to all hotspots in the study area.

*Procedure intervention:*

Compounds in intervention clusters that have been selected for the intensive malaria control will be visited in January-February for mapping, to update census lists, (appendix C) and explain the study procedures.

*Larviciding*

Persistent breeding sites will be mapped using handheld GPS systems in all clusters. In the period preceding the long rainy season (March-April 2012), all permanent aquatic habitats inside hotspots and those located on the fringe of hotspots but are a likely source of anophelines in hotspots based on expert opinion, will be treated at weekly intervals with approved larvicides (*Bacillus thuringiensis var. israelensis* (Bti) and/or *Bacillus sphaericus* (Bs). Within a hotspot all mapped water bodies will be treated by trained personnel and any other non-mapped water bodies will be dipped to search for *Anopheles* larvae and also treated if larvae are found. One week later the area will be revisited and all water bodies dipped again for anopheline larvae. Any positive sites will be treated. This will continue throughout the transmission season (May – July 2012).

Mapping of all persistent breeding sites will be used to initially locate sites within hotspots for larviciding and secondly to calculate distance to breeding sites from study compounds both in intervention and control clusters. This is necessary to take into account variability in distribution of breeding sites whether treated or not.

*Indoor residual spraying*

The insecticide that will be used for IRS will be decided on following consultations with DOMC and will be one of the following: lambdacyhalothrin, alphacypermethrin or deltamethrin. Activities and actual spraying will be undertaken by study personnel; IRS will be timed before the peak transmission season in March, at the time-point that is deemed most efficacious by comprehensive malaria transmission models [19] and again after 6 months.

Heads of compounds will be visited by the study team and consent sought. Compounds where the head, or someone with the authority to provide consent, is absent will be visited for a maximum of three times to maximize IRS-coverage in the hotspots. The study team will remove all movable items from the structures that will be sprayed. Any large items that cannot be removed will be moved into the centre of the room and covered with plastic sheets. Sprayers will use protective clothing, masks and gloves and will dispense the insecticide using a back pack sprayer. The walls and roof of all structures in the compound (residential and non-residential) will be sprayed for at least 15 minutes according to guidelines for the insecticide used. The structures will be left locked for 2 hours after which the doors and windows will be opened and allowed to air out for 30 minutes. After this the head of the house may enter to sweep clean. During the government-led IRS program of 2011 lambda-cyhalothrin was used and was reported to occasionally result in itching. Approximately 1 week after the spray households will be revisited to interview members on any reported side effects (see appendix F& H).

Spraying will be repeated at 6-monthly intervals (visits 1 and 3).

*Long-lasting insecticide treated nets distribution*

At the point of the census study staff will document the number of sleeping spaces within each house. At the time of the intervention (March 2012), the study team will distribute one LLIN for each sleeping space within the house, hang the net and explain the proper use and maintenance of the net. All study nets will be labelled for later identification. To avoid potential irritation to the insecticide used in the LLIN, nets will be hung outside for at least 24 hours before being distributed to communities to allow the strength of the insecticide to wane.

During a second visit, one month after initial LLIN distribution the correct usage of LLINs will be evaluated: the correct hanging of LLINs will be confirmed and household members will be asked to explain how they use the net. If needed, instructions about correct use will be repeated and additional nets can be provided if nets are missing or found to be torn. A third visit will occur to re-assess the quality and use of the nets 6 months after the first visit, in conjunction with the second round of IRS. At this point new ownership and quality will be re-assessed and new nets will be distributed as needed. All information on net use and quality will be recorded (appendix D).

*Focal Screening and Treatment (FSAT)*

Screening of a sentinel population within households

The FSAT utilizes individuals aged 6 month to 20 years as a sentinel group to indicate malaria exposure in the household because this age-group experiences the highest parasite burden [23-24]. For this age group all individuals will be tested for parasites using RDTs regardless of presence of symptoms or not. However clinical care will not be restricted to just this age group. All age groups may experience clinical malaria in our setting ([name] *et al.*, in preparation) and therefore those individuals over 20 years who are found to have fever will also be tested by RDT and receive treatment as oart of the FSAT intervention.

The FSAT campaign will take place in intervention hotspots in March 2012; a second round of FSAT is planned to take place in September 2012. Both campaigns will follow identical procedures.

Screening the sentinel group

Blood samples will be collected from all individuals aged between 6 months and 20 years. Blood will be collected by fingerprick and used to test for malaria by rapid diagnostic test (Premier Medical First Response Combo^®^,HRP-2 & LDH based), for determination of haemoglobin levels using a Copack Colour Scale ® (Oststeinbek, Germany), to prepare a microscopy slide and to collect blood into an EDTA microtainer tube and onto a filter paper. RDTs will be used for clinical decision-making; slides will read after the campaign to determine the relative sensitivity of RDTs and PCR in the study setting. The Copack Haemoglobin Colour Scale system has been available since 2001 and is a reliable and validated method to assess haemoglobin levels. The test consists of a drop of blood being placed on the test strip, and after 30 seconds is compared to the hue on the provided colour scale. The gradient of the colour scale indicates whether and how severely anaemic a person is with the scale ranging from <4 to 14 g/dl of haemoglobin. The collected blood samples will be analysed for parasite prevalence by microscopy PCR and the detection of malaria-specific antibody responses by ELISA (see section g: laboratory analyses).

Screening the non-sentinel group

In addition to testing the sentinel age-group, all other individuals aged above 20 years will have their temperature by ear thermometer and blood samples taken by fingerprick. Those that are febrile (as defined by the range of the specific thermometer used) will be tested for malaria using RDTs otherwise blood will be collected as described above for the same purposes.

Using the sentinel population to detect microscopic and submicroscopic parasite carriers

If no parasites are detected in the sentinel age group, it is unlikely that any parasite carriers are present in the household. If, on the other hand, one or more participant between 6 months and 20 years are parasite positive, it is likely that household members are also infected. Household members of malaria-infected individuals are up to 10-fold more likely to be infected with malaria themselves [2, 25][Mosha *et al.*, unpublished findings]. This household clustering of infections often occurs below the threshold density that allows infections to be detected by microscopy or RDTs. In other words, in households where somebody carries parasites as confirmed by RDT, there is highly significant clustering of low density infections that are negative by RDT and slide but positive by PCR [14, 25]. Up to 50% of all infections may be missed by RDTs or microscopy in settings like the Kenyan highlands because the density of infections is often very low [14]([name], in preparation). These asymptomatic low-density infections are clinically and epidemiologically relevant and can result in chronic anaemia and continued malaria transmission [35].

Treatment once parasites are detected in a household

We will give all people who reside in the same house as anyone (in the sentinel or non-sentinel group) found to be RDT positive a complete curative dose of antimalarials to clear parasite densities, except those under 6 months of age and pregnant women (see below), This focal treatment of parasite carriers in hotspots will maximize the impact of FSAT [26] since it includes symptomatic and asymptomatic, microscopic and submicroscopic parasite and gametocyte carriers. A proportion of those people who stay in the same house as parasite carriers will be themselves be free of detectable parasites at the moment of FSAT. Since there is currently no molecular assay that can detect these sub-microscopic infections in field settings, our approach is the only operationally feasible way to include microscopic and sub-microscopic parasite and gametocyte carriers without exposing individuals who are exposed to low malaria risk (i.e. those living outside hotspots of malaria transmission) unnecessarily to antimalarial drugs. In line with this, our approach should not be interpreted as mass drug administration since our treatment is restricted to small (<1km^2^) areas with proven high exposure to malaria.

Treatment will be carried out using artemether-lumefantrine (Coartem, AL) according to national guidelines. AL is an antimalarial drug with an excellent safety profile; limited data on safety are available for children under 6 months and pregnant women, both groups will therefore be excluded from AL treatment (see below) but receive clinical care when necessary. As detailed below, all those who are given Coartem will be actively followed-up to monitor any side effects. This monitoring will happen on all days of treatment and one week after the start of treatment. If given to parasite-free individuals, AL will provide an effective prophylactic effect for 3-4 weeks, which has been shown to be highly beneficial for malaria control purposes in high endemic regions [36]. In parasite carriers, AL effectively clears asexual parasites and gametocytes, the parasite stage responsible for transmission [35]; the timing of FSAT is chosen to ensure individuals are parasite and gametocyte-free before the start of the peak transmission season. For those receiving AL, the first dose will be supervised and then instructions will be provided for taking of the second dose which will be issued. Teams will return to compounds the next day to administer and supervise the third dose and distribute the fourth. They will return again on the third treatment day to again administer and supervise the fifth dose and distribute the sixth. At the same time any side effects will be noted. (see appendix G & H).

All participants will be told their haemoglobin level immediately, and any person found to be anaemic will be provided haematinics according to national guidelines.

Treatment of risk groups: children <6 months and pregnant women

Children below 6 months of age will be excluded from the study; they will be screened for fever and referred to a health facility where needed but will not be included in FSAT.

Pregnant women will not receive AL. Prior to consent and treatment, it will be explained why AL cannot be given to pregnant women and therefore the necessity to assess whether women of childbearing age may be pregnant if anyone in their household is found to be positive for malaria. Women may opt not to be tested for malaria. In each survey team there will be a female field worker trained to carry out interviews and test for pregnancy. She will approach women of childbearing age (13-45 years) in households where there is ≥1 parasite positive participant. These women will be asked whether they could be pregnant, and the date of their last menstrual period. Women whose last menstrual period was not within the prior 4 weeks, and/or who could be pregnant will be asked whether they would be willing to perform a pregnancy test on their urine sample. A recent survey of houses in the study area showed all to have pit latrines where a urine sample can be collected and a pregnancy test can then be conducted by the field worker away from the house. Women will be provided results of their pregnancy test in a private area in a confidential manner. This was shown to work in a sister study (SSC 1517). Confidentiality will be ensured at all times. Females whom have a negative pregnancy test can be given AL.

Women with a positive pregnancy test or those who would rather not have a pregnancy test performed will be offered a test for malaria parasites by RDT. If a woman who is pregnant or may be pregnant is parasite positive by RDT, she will be offered to be taken to a nearby health facility for examination and appropriate treatment before being returned home. If a women who is pregnant or may be pregnant is parasite negative by RDT, she will be asked about her last dose of intermittent preventive treatment in pregnancy (IPTp) with sulphadoxine-pyrimethamine (SP) and her antenatal records will be consulted. If the IPTp dose of SP was given <4 weeks ago, no additional treatment will be given. If the dose is >4 weeks ago or a woman has never received IPTp and the woman is eligible for a dose of SP according to national guidelines, she will be offered to be taken to a nearby health facility for examination and appropriate treatment before being returned home. All costs incurred by the woman will be covered by the project.

As part of the supervisory team a qualified Clinical Officer will be available to advise on all treatment regimes and any side effects from drugs taken.

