**3. ABSTRACT:**

The burden of malaria is not equally distributed in Kenya. Some villages experience a higher exposure to malaria compared to neighbouring villages and even within villages some households are disproportionally affected. In the Rachuonyo district in the Kenyan highlands, this heterogeneity in malaria exposure is striking with parasite prevalence rates at schools ranging from 0% to >70%. The persistence of malaria in small geographical areas despite high coverage with insecticide treated nets (ITNs) and indoor residual spraying (IRS) may be partially explained by outdoor biting and resting of malaria vectors.

These insights in the micro-epidemiology of malaria transmission in Rachuonyo district suggest that a revision of malaria control strategies may be needed to successfully control and eliminate malaria. In the current study, we propose to determine the value of rolling out four targeted malaria control efforts simultaneously in reducing malaria transmission. These targeted control efforts include local upscaling of currently used IRS and ITNs in hotspots of malaria transmission. In addition, larviciding will be employed to target malaria vectors, also those that are less susceptible to IRS and ITNs as a consequence of outdoor feeding and resting. Lastly, the human infectious reservoir will be reduced by treating parasite carriers and their household members in hotspots of malaria transmission.

The impact of these targeted interventions will be assessed in the context of currently ongoing malaria control activities in a 2-year cluster randomized trial. In the cluster randomized trial up to 8 interventions clusters will be randomized to receive hotspot targeted interventions and compared with an equal number of control clusters where the (untargeted) malaria control activities continue. The intervention will be evaluated based on changes in parasite prevalence measured in community surveys inside and outside hotspots of malaria transmission.

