**9. DESIGN AND METHODOLOGY:**

## a. General study design

This study is a cluster-randomized trial where we compare the impact of hotspot targeted interventions on malaria transmission. Up to 16 clusters will be defined based on currently ongoing activities with half receiving the interventions. In each of the intervention clusters, all 4 hotspot-targeted interventions will be superimposed on ongoing control measures: hotspots will be targeted with a combination IRS, LLINs, larviciding and FSAT. The other clusters will serve as controls; these areas will not be targeted.

The interventions will be evaluated in the context of ongoing malaria control efforts. In the entire study area current ongoing malaria control interventions will continue without interruption.

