## g. Procedures: evaluation phase

**Community cross-sectional surveys**

*Consent procedure cross-sectional surveys:*

As with the intervention phase, meetings will be organised with the district commissioner, officers and chiefs with the district health team to seek approval for the evaluation phase. Sensitization of communities will be done by chiefs and assistant chiefs and village elders from the study area. Community meetings (barazas) will be held in the selected areas and study staff will explain the purpose of the surveys, the procedures to be followed and the risks and benefits of participation. Information sheets shall be provided in English, DhoLuo, or Kiswahili to all district representatives, chiefs and households (Appendix A).

Households will be informed at the barazas of the timing of the survey and that their compounds may be visited.

On the day of the cross-sectional survey informed consent will be obtained at the individual level. All consent forms will be available in English, DhoLuo, or Kiswahili. Translations will be checked through back-translation (Appendix B). Consent will be obtained by signature or thumb-print accompanied by the signature of an independent witness of selected individuals and/or their parents/guardians. Assent forms will be signed by children between the ages of 13 and 17 years and by their parents/guardians. Each assent form will be accompanied by consent form signed by the parent/guardian.

*Timing of the cross-sectional surveys:*

Six cross-sectional surveys will be conducted (see table in section 11):

- Pre-transmission season (March 2012)
- Peak transmission season (June 2012)
- Post transmission season (September 2012)
- Pre-transmission season (March 2013)
- Peak transmission season (June 2013)
- Post transmission season (September 2013; final survey)

*Procedure cross-sectional surveys:*

Prior to the surveys, census lists for all hotspots will be updated using PDAs, recording the name, age and gender of each household occupant (see appendix C for summary of information collected). For each cross-sectional survey up to 100 individuals above the age of 6 months will be randomly selected from malaria hotspots and up to 500 participants above the age of 6 months will be randomly selected from outside malaria hotspots in each cluster. Randomization will occur at the compound level.

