Intervention participants will receive intensive malaria control for their household: IRS, LLINs, larviciding and in FSAT. These interventions are expected to have a direct and an indirect beneficial effect on the level of malaria the household is exposed to: IRS will reduce indoor mosquito exposure, LLINs will protect individuals from (infected) mosquito bites, larviciding will reduce indoor and outdoor mosquito exposure; FSAT will clear parasite carriage and provide 3-4 weeks of efficacious prophylaxis against malaria infections. These interventions are provided free of charge.

The wider community, i.e. those living in the vicinity of hotspots will not receive any direct benefits from the interventions, but are likely to experience indirect effects. Reductions in neighbouring areas with high malaria prevalence may result in reduced malaria transmission in the wider region.

*Benefits to participants in control area*

Participants in the control areas will not benefit from the interventions in the short term but will benefit from free screening and treatment for symptomatic malaria. However, the information that will be learned as a result of this study can benefit them in the future through more effective and targeted malaria control interventions and the possible overall reduction in malaria transmission that may ensue. There are plans for district-wide government-led interventions such as IRS to take place. All these will continue as planned and none will be withheld from the communities. Depending on the outcomes of the first year of the intervention, in consultation with the DOMC, to roll-out the most efficacious intervention/s to all hotspots in the study area.

*Community benefits*

The community benefit of the project is that we expect malaria transmission in the entire area to be reduced as a result of our hotspot targeted interventions. Free LLINs and intensive vector controlled will be offered to individuals residing in some of the strongholds of malaria transmission in Rachuonyo district; plausibly leading to a direct benefit to this part of the population that is most affected by malaria. The MOH is also expected to benefit from this study by gaining a lot of information on the status of malaria transmission in this area of Rachuonyo district as the findings will be shared with them. The Government of Kenya may also benefit by improving malaria control strategies and targeting efforts where they can be most effective.

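### The aim of rolling out the most efficacious component(s) to all hotspots after year 1 asks for a ranking the bundled design cannot give, and would weaken or remove the later randomised contrast

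*Protocol*

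**What the plan says.** The abstract describes a "2-year cluster randomized trial". Section 9a gives the intervention arm one content: "In each of the intervention clusters, all 4 hotspot-targeted interventions will be superimposed on ongoing control measures". The paragraph on routine control in the control clusters states that they receive no hotspot-targeted measures.

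Section 9g schedules six surveys, in March, June and September of 2012 and of 2013. The last is listed as "Post transmission season (September 2013; final survey".

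Section 9f then adds a step that would change the control arm: "Depending on the outcomes of the first year of the intervention, in consultation with the DOMC", the team would extend what worked, in that "we aim to roll-out the most efficacious intervention/s to all hotspots in the study area". Section 12b repeats the aim ("to roll-out the most efficacious intervention/s to all hotspots in the study area") under the benefits to participants in the control area, which confirms that control hotspots are meant.

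Neither place gives a date, a triggering result, a survey that must finish first, or the status of surveys that come after. The data analysis part of section 10 names PCR-confirmed parasitaemia as the primary outcome but does not tie it to a survey.

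**The concern.** There are two separate difficulties.

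The first is identification. The roll-out sentence presumes that one year of data will show which intervention or interventions did best. A trial of one four-part package against no targeted measures yields one randomised contrast. Any choice among components would have no randomised basis.

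The second is the control arm. The intervention hotspots are already treated, so extending measures to every hotspot can only add the control hotspots. From then on, a comparison by allocated arm no longer sets the package against untargeted control, and an analysis that treats it as such is biased toward no effect. The roll-out depends on first-year results, so a favourable first year is presumably what would bring it about. The second-year contrast would then be lost in the circumstances in which the trial most needs it. The protocol does not protect a comparison made before that step.

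**Working it through.** **Component ranking.** No arithmetic is needed. Section 9a gives the treated arm four measures in every cluster, and the control arm has none of them in targeted form. Two arms give one estimable difference, while four component effects would have to be separated. They cannot be.

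**Which surveys are exposed.** Section 11 places net distribution and screening-and-treatment at the same time as the March survey, with spraying and larviciding immediately after it, in 2012 and 2013.

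- March 2012 is the baseline; June and September 2012 fall within year 1. All three are unaffected.
- March 2013: if roll-out keeps this calendar, it coincides with or follows the survey, so the survey remains largely a 12-month comparison. This holds above all in the evaluation zone, where any effect is indirect. It is exposed only if roll-out comes earlier.
- June and September 2013: exposed under any roll-out up to March 2013.

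**Size of the dilution.** Inputs from section 9e: evaluation-zone prevalence p0 = 10% versus p1 = 5%, m = 300 people per cluster, k = 0.5, 8 clusters per arm. The values 1.96 and 0.84 are stated for the inside-hotspot calculation and assumed to apply here too.

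Variance term: V = p0(1−p0)/m + p1(1−p1)/m + k²(p0² + p1²).

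*The plan's own figure first.* V = 0.000300 + 0.000158 + 0.25 × (0.0100 + 0.0025) = 0.003583. Clusters per arm = 1 + (1.96 + 0.84)² × 0.003583 / 0.05² = 1 + 11.24 = 12.2, so 13. The stated 8 does not reproduce at k = 0.5; it fits k of about 0.35 (7.25, rounded up to 8). That is a separate issue. It matters here only because the starting power at 8 per arm and k = 0.5 is below 80%.

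*Power at 8 per arm.* Two-sided t-test with 14 degrees of freedom and non-centrality (p0−p1)/√(V/8).

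- With no control gain: 0.05/√(0.003583/8) = 2.36, power 59%.

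*After roll-out.* Let f be the share of the full effect that control clusters gain. The documents do not give f, so it is varied from 0 to 1. Control prevalence becomes 10% − 5% × f.

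- At f = 0.5, control prevalence is 7.5%. V = 0.000231 + 0.000158 + 0.25 × (0.005625 + 0.0025) = 0.002421. Non-centrality = 0.025/√(0.002421/8) = 1.44, power 27%.

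| f | Control prevalence | Difference (points) | Power, one survey |
|---|---|---|---|
| 0 | 10% | 5.0 | 59% |
| 0.25 | 8.75% | 3.75 | 44% |
| 0.5 | 7.5% | 2.5 | 27% |
| 0.75 | 6.25% | 1.25 | 12% |
| 1 | 5% | 0 | rejection at the alpha level only |

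The normal approximation, using c − 1 in place of c, gives 60%, 45%, 27% and 11% for the first four rows. With k = 0.35 that approximation gives 84%, 68%, 43% and 16%. The starting level depends on k; the shrinkage of the difference does not.

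**The case against.** The roll-out is an aim, conditional on results and on consultation with the national programme, and it has no date. It may not happen, or may happen after September 2013. Because it depends on first-year outcomes, June and September 2012 should precede it. The primary time point may also be fixed in a statistical analysis plan that is not at hand. All of this stands. It limits the point to a conditional risk, and the lack of a named primary survey is not itself the finding.

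Several stronger readings are tempting and are not supported:

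- A reader might infer that roll-out would end the contrast before all three 2013 surveys. The text gives no such date, and the section 11 calendar would leave March 2013 largely intact.
- A reader might infer that the contrast necessarily vanishes. The wording allows only some components to be extended. The comparison would then be package versus part-package, which is diluted but not gone.
- A reader might quantify the loss by averaging the five post-baseline surveys. The protocol specifies no such average.
- A reader might call the later data non-randomised. The clusters stay randomised, to early versus delayed intervention; what changes is the question answered.

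Two things are not answered by these objections. An analysis plan cannot recover component effects that the design does not contain. And the order of survey and roll-out is a rule of conduct that must be settled in the field before the analysis. The protocol itself sets an untargeted control arm beside an aim to target it.

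**Conclusion.** The point holds in a limited, conditional form. First-year data can support a decision on the four-part package only, so the stated basis for choosing components is wrong as written. If roll-out follows year 1, at least June and September 2013 lose or dilute the intervention-versus-control contrast, and March 2013 does too if roll-out comes earlier than the section 11 calendar. The 2012 surveys stay valid.

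Under the section 9e assumptions with 8 clusters per arm, a single later survey goes from 59% power to about 27% if controls gain half the effect, and to no contrast if they gain all of it. These figures rest on an assumed control gain and illustrate the risk; they do not forecast it. Because the step is conditional and year 1 is unharmed, this is something that should be fixed. It does not defeat the trial.

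**What to change.** Three changes of wording in sections 9f, 9g and 10, with section 12b kept consistent:

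1. Name as the confirmatory comparison a survey that must be completed in all clusters before any control hotspot is offered the interventions.
2. State that, if roll-out occurs, later surveys compare early with delayed intervention and are not used as the intervention-versus-control result.
3. Replace the choice of the most efficacious component(s) with a decision on the four-part package as a whole.

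This needs no extra fieldwork and leaves the possibility of a roll-out after year 1 open. The cost is that second-year data lose confirmatory status if roll-out goes ahead. Deferring roll-out until after September 2013 would also protect the contrast, but it would alter what section 12b holds out to control communities. That is a trade-off for the investigators and the ethics committee, and this point does not depend on it.
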